### 2.3. Sample Size Calculation

Based on machine learning model requirements for predictive validity with categorical variables, a minimum of 50 samples per category is deemed necessary [22,23,24,25]. Considering potential variability and ensuring sufficient data for model training and validation, we aim to recruit 100 patients with FD.

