### 2.7. Data Collection

Pattern identification will be conducted by licensed Korean medicine doctors via questioning, tongue diagnosis, pulse diagnosis, and abdominal diagnosis. This assessment determines deficiency–excess, cold–heat, and the presence of phlegm or food stagnation, as well as six primary FD differentiation patterns (spleen and stomach deficiency–cold, spleen Qi deficiency, liver–stomach disharmony, food stagnation, spleen deficiency with damp–heat, mixed cold and heat).

Bio-signal measurements will be conducted during the second visit or during the first visit only if the screening procedures confirm that the participants meet the inclusion criteria. Prefrontal cortex activity will be measured using a headband-type fNIRS device (NIRSIT; OBELAB Inc., Seoul, Republic of Korea). SCR, ECG, and pulse wave signals will be recorded with electrodes attached to the fingers, wrist, and chest, connected to the Biopac MP160 system (BIOPAC Systems Inc., Goleta, CA, USA). Radial artery pulse waves will also be measured using the DMP-LIFE PLUS pulse analyzer (DAEYOMEDI Co., Ltd., Ansan, Republic of Korea). These measurements will be conducted with the participants in supine position for two minutes. To maintain objectivity, the researcher measuring biometric signals will be different from the doctors diagnosing the patients with FD. Additionally, the diagnosis and pattern identification results will be blinded to both the researcher and the participants. Throughout the measurements, participants will be monitored thoroughly for any discomfort or adverse events.

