Additionally, we will investigate local and relative differences in brain activity through amplitude and frequency power analysis. Frequency-domain techniques (e.g., Fast Fourier Transform (FFT), Short Time Fourier Transform (STFT), and wavelet transforms) can be applied to extract spectral features from bio-signals, capturing power distributions across key frequency bands [44]. Recent hybrid approaches transform time-frequency representations into image-like inputs, enabling the use of CNN-based models to automatically discern frequency-related patterns. These methods can be used to enhance the sensitivity of diagnostic tools, particularly for complex and non-stationary bio-signals [45]. The significance and validity of the model will be assessed based on the classification accuracy and the area under the receiver operating characteristic (ROC) curve. These metrics will be obtained through bootstrapping and cross-validation methods and tested against a chance level (0.5, 0.33, or 0.17, depending on the prediction outcomes) using a *t*-test with a significance level of *p* < 0.05.

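### The chance levels 0.5, 0.33 and 0.17 are the wrong benchmarks for a multi-class AUC, and for accuracy when patterns are unequally frequent, so models with no signal can pass

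*Protocol article*

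**What the plan says.** The last part of section 2.8 (Statistical Analysis) states how a model will be judged. Its significance and validity are "assessed based on the classification accuracy and the area under the receiver operating characteristic (ROC) curve". The next sentence begins "These metrics will be obtained through bootstrapping and cross-validation methods and tested against a chance level"; both metrics are thus "tested against a chance level (0.5, 0.33, or 0.17, depending on the prediction outcomes"), with the level chosen by prediction outcome. The test is a t-test at the 0.05 level; sidedness is not stated.

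The outcomes are described in section 2.7 (Data Collection). The Korean medicine doctors assign "six primary FD differentiation patterns", which matches the level 0.17. Of the other outcomes the section says: "This assessment determines deficiency–excess, cold–heat, and the presence of phlegm or food stagnation". It does not give their number of levels; two or three can be inferred from 0.5 and 0.33.

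Section 2.3 (Sample Size Calculation) says "we aim to recruit 100 patients with FD". Section 2.5 (Participant Recruitment) describes open recruitment by postings, posters and flyers, with no quota by pattern.

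**The concern.** One list of null values serves two metrics whose no-information values differ.

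- **AUC.** This is a ranking measure. Scores unrelated to the label give 0.5 in each one-vs-rest or pairwise comparison, and so 0.5 on average over classes, however many there are. A null of 0.33 or 0.17 lies well below what noise achieves.
- **Accuracy.** 1/K is what uniform guessing scores. A fitted classifier can learn class frequencies, and with no signal in the predictors it can score the share of the commonest class simply by always naming it. That share exceeds 1/K unless all classes are equally frequent.

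This is the only criterion for model success that the article states. If the benchmark is too low, a model that makes no use of the bio-signals could be reported as significantly better than chance, which is the opposite of what the study sets out to show.

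**Working it through.** **Inputs.** From the article: N = 100 (2.3); null values 0.5, 0.33 and 0.17, a t-test and α = 0.05 (2.8); K = 6 for the primary patterns (2.7). Assumed: K = 2 and 3 for the other levels; the pattern frequencies, which the article does not give; and a two-sided t-test, counted as a pass only when the result lies above the null.

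**Step 1: reproduce the stated levels.** 1/2 = 0.500, 1/3 = 0.333 and 1/6 = 0.167, which round to 0.5, 0.33 and 0.17. The stated levels are therefore 1/K, the accuracy of uniform guessing.

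**Step 2: AUC without signal.** Random scores were drawn for 100 patients in 2000 runs. On the whole sample, macro one-vs-rest AUC had mean 0.50, with SD 0.035 for K = 3 and 0.033 for K = 6 (lowest value for K = 6: 0.38). A t-test over 5 stratified cross-validation folds, across several assumed class frequencies, gave these shares of noise runs declared better than chance:

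| K | Against the stated level | Against 0.5 |
|---|---|---|
| 2 | 2–3% (stated level is 0.5) | 2–3% |
| 3 | 85–93% (0.33) | 2–3% |
| 6 | 100% (0.17) | 3% |

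The nominal rate in the favourable direction is 2.5%. The result for 0.33 and 0.17 does not depend on unequal frequencies: with equal classes it was 93% and 100%.

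**Step 3: accuracy without signal, exact test.** With class shares p_k, always naming the commonest class scores max(p_k) in expectation. If it gets x of 100 right, the one-sided p-value against 1/K is P(X ≥ x), with X binomial (100, 1/K).

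| Null | Assumed share of commonest class | p |
|---|---|---|
| 1/2 | 55% | 0.18 |
| 1/2 | 60% | 0.028 |
| 1/2 | 70% | <0.0001 |
| 1/3 | 40% | 0.097 |
| 1/3 | 50% | 0.0004 |
| 1/6 | 20% | 0.22 |
| 1/6 | 22% | 0.10 |
| 1/6 | 25% | 0.022 |
| 1/6 | 30% | 0.0007 |
| 1/6 | 40% | <0.0001 |

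**Step 4: accuracy without signal, t-test over folds.** This is closer to the planned test. It used 10 stratified folds and 2000 runs, with no information in the predictors. Share of runs passing against the stated level:

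| K | Assumed share of commonest class | Always naming the commonest class | Guessing in proportion to frequency |
|---|---|---|---|
| 2 | 55 / 60 / 70% | 81 / 96 / 100% | 4 / 8 / 41% |
| 3 | 40 / 50 / 60% | 95 / 99.8 / 100% | 6 / 19 / 61% |
| 6 | 25 / 35 / 45% | 99.6 / 100 / 100% | 5 / 29 / 64% |

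Uniform guessing passed in 1–3% of runs throughout. It is the rule for which 1/K is the right null.

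**Step 5: is the null the only fault?** With truly equal classes, the majority rule still passed the fold-based t-test in 69% (K = 2), 76% (K = 3) and 85% (K = 6) of runs. Sample frequencies vary around equality, and fold accuracies under that rule have very little spread. Values from cross-validation or bootstrap replicates are also not independent. Replacing the null value alone would therefore not fully repair the test.

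**The case against.** The sentence is condensed, and the authors may have meant 0.5 for AUC and 1/K for accuracy. The wording does not say so: it ties the level to the outcome and applies it to both metrics. If that was the intention, the sentence still needs correcting and the accuracy problem remains.

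For a two-class outcome, 0.5 is the correct AUC null, and some of the outcomes may be binary. That stands: the AUC error is confined to 0.33 and 0.17. The article also does not say how a multi-class AUC is averaged. A micro-averaged AUC can exceed 0.5 without signal when classes are unequal, which moves the null further from 0.33 and 0.17, not closer.

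The accuracy half depends on frequencies the article does not give. Unequal sizes are likely under open recruitment but not certain. By the exact test, mild imbalance does not produce a false pass (55% against 1/2, 40% against 1/3, 20–22% against 1/6). That limits the size of the error. It does not make 1/K the right null for a fitted classifier on raw accuracy.

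Class weighting or resampling may be specified in a fuller document, and their absence here is not held against the plan. The point rests on null values that the article does state.

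**Conclusion.** The concern holds as stated.

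- **AUC.** Levels of 0.33 and 0.17 are invalid nulls whatever the pattern frequencies. Noise passed in 85–93% and 100% of simulated runs, against a nominal 2.5%. These rates assume macro one-vs-rest AUC and a t-test over five folds; another resampling scheme would change the figures but not the conclusion.
- **Accuracy.** 1/K is valid for a fitted classifier only with equally frequent patterns. The size of the error depends on assumed shares. With six patterns, a commonest share of 25% already yields p = 0.022 for a rule that ignores the bio-signals; at 20–22% the exact test does not reject.

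Because this is the stated threshold for model success, it should be corrected before the models are evaluated.

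**What to change.** In section 2.8, replace the single list of chance levels with a null for each metric:

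1. **AUC:** null value 0.5 for every outcome, with the multi-class AUC named as macro one-vs-rest.
2. **Accuracy:** either balanced accuracy against 1/K, or raw accuracy against the observed share of the commonest class (the no-information rate). Choose one in advance.
3. **p-values:** take both from a label-permutation distribution, rerunning the whole cross-validated procedure on each permuted data set, in place of the t-test over replicates. Permutation keeps the observed class frequencies and does not treat dependent replicates as independent, so it also deals with the fault in step 5.

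The cost is a short rewording of the last part of section 2.8 and more computing time for the permutations. No further patients or measurements are needed. The benchmark becomes harder to beat: under the assumed frequencies in step 4, the accuracy null rises from 0.5 to 0.55–0.70 (K = 2), from 0.33 to 0.40–0.60 (K = 3) and from 0.17 to 0.25–0.45 (K = 6).

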### 2.9. Participant Safety

All participants will be thoroughly informed of the study’s purpose, procedures, potential risks, and benefits before participation. Written informed consent will be obtained from each participant. Given that the study involves only non-invasive biometric measurements using electrodes and surveys, no adverse reactions are anticipated. However, if a participant experiences any discomfort or adverse events before or during the measurements, the study will be halted immediately. The researcher will monitor the participant’s condition and decide whether to continue the study. If the researcher’s judgment is insufficient, the principal investigator will make the final decision regarding study termination for that participant.

In the event of a serious medical situation during the study, the procedure will be stopped immediately, and appropriate measures will be taken. The incident will be reported to the Institutional Review Board (IRB), and emergency care will be provided at Kyung Hee University Hospital in Gangdong as needed.

## 3. Discussion

This study represents an initial step toward enhancing the objectivity and reliability of pattern identification in patients with FD through the integration of brain–body bio-signals into AI-based diagnostic algorithms. While our current protocol focuses on collecting bio-signals, such as fNIRS, SCR, ECG, and pulse wave under controlled clinical conditions, future advancements are expected to extend beyond these boundaries. Ongoing progress in sensor miniaturization, wearable device technologies, and AI-driven analytics suggests a more integrated and dynamic approach to patient care.

As sensor technology becomes increasingly compact and accessible, it will likely become feasible to gather data outside the clinical setting. For instance, wearable sensors capable of continuously monitoring autonomic activity, subtle variations in pulse waves, or low-level cortical signals can support more naturalistic and longitudinal assessments of patients with FD. By capturing changes in symptoms, lifestyle factors, medication responses, and dietary habits in real-life contexts, these wearable systems may facilitate the early detection of subtle pattern shifts, allowing for timely intervention before symptoms become clinically significant.

The role of advanced AI techniques—such as deep learning and multimodal data fusion—will continue to grow. Integrating signals from multiple physiological domains enables AI models to detect complex patterns that conventional analyses may overlook. Over time, these insights may relate specific brain activities and autonomic responses to FD-associated patterns, thereby refining the conceptual framework of pattern identification in Korean medicine. Such evidence-driven approaches could also contribute to establishing more standardized and reproducible diagnostic criteria, maintaining a balance between traditional clinical expertise and quantitative precision. For instance, integrating brain–body bio-signals with AI algorithms has shown effectiveness in diagnosing subjective pain reports [16,17]. Additionally, when bio-signals are paired with machine learning techniques, they can be utilized to diagnose emotional states such as anxiety [46], pleasure, fear, and anger [47].

In the long term, we anticipate incorporating these technologies into a comprehensive Korean medicine-based health check-up system. By combining time-honored diagnostic insights with state-of-the-art bio-signal analytics, patients could benefit from more personalized and preventive care. Regular assessments—either periodically within clinical environments or continuously via wearable devices—would generate robust data sets, guiding timely interventions, individualized herbal prescriptions, acupuncture treatments, and lifestyle recommendations. Such an initiative could improve patient outcomes, enhance quality of life, and reinforce global confidence in Korean medicine as a scientifically grounded, patient-centered practice.

While using bio-signal measurements as diagnostic tools offers several advantages, there are potential limitations to consider. Firstly, the controlled experimental setting for collecting bio-signal data may not fully capture the variability of symptoms that patients experience in their everyday environments. For instance, FD patients may experience symptoms after meals, which can diminish over time and potentially affect their bio-signals. To address this issue, we will assess the severity of FD symptoms at the time of bio-signal measurement using a Visual Analog Scale (VAS), in addition to the questionnaires. Secondly, despite the integration of multiple bio-signals, accurately correlating these signals with specific FD patterns is inherently complex due to the multifactorial nature of the condition. Multi-collinearity should also be accounted for during data analysis.

In summary, while our current research protocol marks an important step toward quantifying and objectifying FD pattern identification through bio-signals and AI, further developments extend well beyond the present scope. Enhanced sensor technologies, wearable integration, and advanced AI analytics, combined with a holistic Korean medicine health check-up model, hold the potential to transform FD management. This integrated, data-driven strategy may serve as a template for aligning traditional diagnostic principles with cutting-edge scientific methodologies, ultimately offering more nuanced, patient-focused, and effective care.

## Figures and Tables

**Table 1 jcm-14-01072-t001:** Clinical study schedule.

	Visit 1 (Screening)	Visit 2 (Bio-Signal Measurements)
Written consent	●	
Demographic/medical history survey	●	
Vital sign (blood pressure, pulse, temperature) measurements	●	●
Physical measurements (weight, height)	●	
Blood test and electrocardiogram	●	
Visual Analog Scale for dyspepsia/diagnosis of functional dyspepsia (ROME IV)	●	
Confirmation of inclusion/exclusion criteria	●	
Medication history/medication intake survey		●
Questionnaires - Standard Tool for Pattern Identification of FD - Cold–Heat Pattern Questionnaire - Deficiency–Excess Pattern Questionnaire - Phlegm Pattern Questionnaire - Food Retention Questionnaire - Spleen Qi Deficiency Questionnaire - Stomach Qi Deficiency Questionnaire - Nepean Dyspepsia Index - State-Trait Anxiety Inventory - Beck Depression Inventory-II - EeroQqol-5-Dimension		●
Korean medicine diagnosis (interview, tongue diagnosis, pulse diagnosis, abdominal diagnosis)		●
Bio-signal measurements (fNIRS, pulse, SCR, ECG)		●
Adverse events assessment		●
Confirmation of clinical study completion		●

## Data Availability

Data are contained within the article.
